#### Sleep measures

##### *Primary outcome measure*

Insomnia Severity Index (ISI): ISI is a recommended outcome measure in sleep research [23], considered as the gold standard self-report measure of insomnia severity in clinical practice. Its seven items assess symptoms of insomnia such as difficulty falling or staying asleep, satisfaction with sleep, and degree of impairment with daytime functioning. The composite score ranges from 0 to 28 and represents no clinical insomnia (0 to 7), sub-threshold insomnia (8 to 14), insomnia of moderate severity (15 to 21), and severe insomnia (22 to 28). ISI has been validated extensively and has proven sensitive to therapeutic changes [23].

##### *Other sleep measures*

Digital sleep diary: Participants will be asked to provide daily subjective estimates of their sleep for 7 consecutive days in a validated sleep diary [24], documenting their daily function, time of entering bed and lights off, the approximate sleep onset latency after lights off, frequency of and length of awakenings, final wake up and rise time, and subjective sleep quality.

#### Physical and mental health measures

EuroQol EQ5D-5L: The EuroQol EQ5D-5L questionnaire [25] will be used to assess health-related quality of life. Its five items assess mobility, self-care, usual activities, pain/discomfort, and anxiety/depression. Items are scored on a 5-point scale, following the format ‘no problems’, ‘slight problems’, ‘moderate problems’, ‘severe problems’, and ‘unable to’/’extreme problems’ for all items.

Chalder Fatigue Scale: The Chalder Fatigue Scale [26] measures the extent and severity of fatigue in fatiguing illnesses. We will use the Norwegian 13-item version. The items are answered on a 4-point scale ranging from asymptomatic to maximum symptomology, such as ‘Better than usual’, ‘No worse than usual’, ‘Worse than usual’ and ‘Much worse than usual’. The global score may be divided into two dimensions: physical fatigue (items 1–7) and psychological fatigue (items 8–11).

Hopkins Symptom Check List: Mental distress will be measured using the Hopkins Symptom Check List-5 [27], which consists of 5 items assessing symptoms of depression and anxiety. The items are answered on a 4-point scale, and range from ‘Not at all’ to ‘Extremely’.

#### Process evaluation

Nijmegen Motivation List 2: The Nijmegen Motivation List 2 [28] will be used to investigate different aspects of participants’ motivation for treatment: Preparedness and active participation, distress as a consequence of participants’ problems, and doubt and reserved attitude towards treatment, its requirements, or the possibilities of benefiting from it. The questionnaire consists of 34 items, scored on a 6-point Likert scale from 1, ‘Not at all applicable’ to 6, ‘Very applicable’.

Credibility / Expectancy Questionnaire: The Credibility / Expectancy Questionnaire [29] asks about the improvements that participants believe will be achieved as a result of treatment, and how believable, convincing, and logical the treatment seems. Its 6 items are scored on a numerical rating scale from 1, ‘Not at all logical’ to 9, ‘Very logical’.

Treatment Components Adherence Scale: The adherence to key behavioural and cognitive CBT-I treatment components, and their perceived benefits, will be assessed with the Treatment Components Adherence Scale [30]. Its 23 items are scored on 4-point Likert scale from 1, ‘Followed rarely or not at all’ to 4, ‘Followed consistently’.

Treatment evaluation scale: The treatment evaluation sheet [31] asks about the relevance, implementation and perceived safety of treatment. The sheet consists of 11 items scored on a 5-point Likert scale from 1, “Not satisfactory” to 5, “Very good”.

Suggestions for improvements: Participants in the intervention group will be asked, in writing, to answer open-ended questions about what worked particularly well and poorly for them during the CBT-I treatment, and their suggestions for treatment improvements.

Qualitative study: A qualitative study will explore facilitators and barriers of participants’ treatment adherence. Individual semi-structured interviews will be conducted at T2 and T3 with 10–12 participants. The interviews will be based on an interview guide developed to answer: “What motivated you to commence and persist with group-delivered CBT-I in primary care?” (adapted from [32]). Usefulness of treatment aspects and the instigated, upheld and/or abandoned changes will be investigated, as well as the processes or experiences that have influenced participants’ actions in behaviour change, or lack thereof. If possible, participants who dropped out from treatment will be interviewed to investigate the reasons for dropping out and what could have helped them finish treatment. The interview guide consists of nine open-ended thematic questions and allows for new questions to be formulated and added to the interview schedule throughout data collection. Question order will be kept flexible, following the participants’ thoughts and narratives. The interviewer will probe areas of interest to the problem statement through all stages. The interviews will be analysed according to the Framework Method, a method used in multi-disciplinary health research teams [33].

#### Potential moderators and mediators

Brief Horne-Östberg Morningness-Eveningness Questionnaire: The reduced Horne-Östberg-Morningness-Eveningness Questionnaire is a widely used measure of the morningness-eveningness dimension [34]. Its five items refer to rising time, peak time, retiring time, morning freshness, and self-evaluated chronotype. A composite score from 4 to 25. Higher levels of morningness are reflected by higher scores.

Dysfunctional Beliefs and Attitudes about Sleep: Participants’ sleep-related cognitions will be measured using the questionnaire Dysfunctional Beliefs and Attitudes about Sleep-16 [35], which consists of 16 items assessing sleep-related cognitions (e.g., faulty beliefs an appraisals, unrealistic expectations, perceptual and attentional bias).

Ford Insomnia Response to Stress Scale: Sleep reactivity will be measured using the Ford Insomnia Response to Stress Scale [36]. Its 9 items assess the vulnerability to situational insomnia under 9 different stressful conditions (i.e., sleep reactivity). The items are scored on a 4-point scale, ranging from ‘Not likely’ to ‘Very likely’.

#### Resource use and work productivity

We will access national health registry data at T5 and T6, to collect information on the short- and medium-term impact of group-delivered CBT-I on rates of sick leave (accessed from the National Insurance Administration), as well as relevant medication (obtained from the Norwegian Prescription Database) and health resource utilization (obtained from the Norwegian Patient Registry). Linkage to the registry data will be based on the social security number of each participant.

#### Sample size

The average observed change in ISI in published RCTs on the effectiveness of group-delivered CBT-I [37–41] from baseline to post-test was 6.2 points in the intervention group, compared to a 1.4-point change in the control group. This indicates a large Cohen’s *d* effect size of 0.86. However, we chose the medium Cohen’s *d* effect size of 0.50 for the sample size calculation, mostly due to the differences in the number of given CBT-I sessions across studies. Treatment in this RCT includes 4 sessions, while other reviewed studies include 5 [37, 38, 41] and 8 [39, 40] sessions, respectively. It is reasonable to assume that treatment effectiveness may decrease with fewer number of sessions. Further, since this is a pragmatic trial, we will not prevent the control group participants from seeking other forms of treatment during the RCT, nor it is a requirement that the participants do not use sleep medications. Thus, treatment effectiveness in this trial may be assumed to be lower than in the aforementioned RCTs.

A power analysis was carried out using a two-tailed t-test with 5% alpha level and 90% power to detect a medium Cohen’s *d* effect size of 0.50, with an allocation ratio of 2:1 (G*Power, version 3.1.9.6) [42]. The needed sample size was 192 in total. Additionally, to have sufficient power for moderation analyses of chronotype, we carried out a two-tailed t-test with 5% alpha level and 80% power to detect a small to medium Cohen’s *d* effect size of 0.40, with an allocation ratio of 2:1, and accounting for a 30% attrition rate based on dropout rates reported by previous studies [43–46]. The final needed sample size was 292 participants (98 in the control group, 194 in intervention group). Since missing data are unlikely to be an issue when using national registers, we did not undertake any statistical power calculations related to these analyses.

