**Discussion:**

This large-scale pragmatic trial will investigate the effectiveness of group-delivered cognitive behavioural therapy versus waiting list in the treatment of insomnia, generating findings that are generalizable to day-to-day treatment of insomnia in interdisciplinary primary care services. The trial will identify those who would benefit from the group-delivered therapy, and will investigate the rates of sick leave, medication use, and healthcare utilization among adults who undergo the group-delivered therapy.

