#### Randomization

Participants will be randomized to the intervention and control group according to a 2:1 ratio. Thus, groups will be formed quicker with more intervention participants, allowing more CBT-I groups to be formed during the limited timeframe of the trial. Unequal randomization may also facilitate recruitment, as participants may be more likely to enrol if they perceive their chance of receiving the intervention to be greater than being placed on the waiting list. Many participants seek out the treatment themselves and reducing the number of waiting list participants is also desirable for ethical purposes. Finally, more intervention group participants will ensure the conduct of planned moderation and exploratory mediation analyses with increased power. Unequal randomization in similar research has previously been recommended [20–22].

Randomization will be performed by the project leader in a secure digital platform for multicentre clinical studies, eForsk. eForsk is a standalone data management system used for electronic self-report data, developed by the Central Norway Regional Health Authority IT department. The randomization will be based on a computerized allocation sequence stratified on each of the participating centres. This will be generated by a third party, the Clinical Research Unit at the Faculty of Medicine and Health Sciences at NTNU. The project leader will be blinded for the block sizes and the allocation sequence. The project leader and research team will thus not influence the randomization process in any way. An overview of the allocation sequence can be provided by the Clinical Research Unit upon request. Participants and the Healthy Life Centre employees will not be masked to the participants’ group assignment.

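### The 292 target is presented as powering chronotype moderation, but it comes from a two-arm main-effect t-test, so 80% power for moderation is not demonstrated

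*Protocol article*

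**What the plan says.** All references are to the protocol article.

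- **Sample size.** The first calculation, for the primary outcome, gives 192 (d = 0.50, 90% power, 2:1). The second is introduced by its purpose: "to have sufficient power for moderation analyses of chronotype, we carried out a two-tailed t-test with 5% alpha level and 80% power". Its remaining inputs are an "effect size of 0.40, with an allocation ratio of 2:1, and accounting for a 30% attrition rate". The result is 292, given by trial arm as 98 control and 194 intervention.
- **Aims (item ii) and Statistical analysis plan.** Moderation is the question of whether chronotype and other factors alter how well the treatment works. That is a treatment-by-moderator interaction.
- **Potential moderators and mediators.** Chronotype is a composite score from 4 to 25. No cut-off or expected split is given.
- **Randomization.** One reason given for 2:1 allocation is: "Finally, more intervention group participants will ensure the conduct of planned moderation and exploratory mediation analyses with increased power".
- **Abstract, Discussion.** "The trial will identify those who would benefit from the group-delivered therapy".
- **Abstract (Methods) and Background.** Both describe the search for factors that influence effectiveness as exploratory. Aims and Statistical analysis plan do not use that word for moderation.

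**The concern.** A two-sample t-test at the trial's allocation ratio asks whether the arms differ on average. Moderation asks whether that difference changes with chronotype. These are different contrasts, and in general they have different standard errors and effect sizes. A calculation for the first says nothing about the second unless the link between them is stated.

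The moderation calculation is the one that sets the enrolment target, because the primary outcome needed 192 before attrition. The Abstract also promises to find out who benefits. If readers believe the interaction test had 80% power, they may take a null result as good evidence that chronotype does not matter. If true power is low, a significant interaction is likely to be an overestimate.

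**Working it through.** **Inputs.** From Sample size: two-sided alpha 0.05, power 80%, d = 0.40, 2:1, 30% attrition, 98 + 194 = 292. Not in the article and assumed here: the moderator scale, the chronotype split, the meaning of 0.40 as an interaction, and the gain from covariates. Effects are in SD units of the outcome.

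**1. Reproduce the article's figures as a two-arm t-test (noncentral t).**
- d = 0.50, 90% power, 2:1: 64 + 128 = 192, power 90.1%. This matches.
- d = 0.40, 80% power, 2:1: 75 + 149 = 224, power 80.3%.
- Attrition: 75 × 1.3 = 97.5, rounded up to 98; 149 × 1.3 = 193.7, rounded up to 194; total 292. This matches exactly, by arm and in total.

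The number is thus fully explained by a main-effect comparison.

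**2. Completers.** 0.7 × 98 = 68.6 and 0.7 × 194 = 135.8, about 204 in all. This is below 224 because the inflation multiplies by 1.3 instead of dividing by 0.7 (224/0.7 = 320).

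**3. Standard errors at 204 completers.**
- Arm comparison: √(1/68.6 + 1/135.8) = 0.148.
- Interaction with a continuous score, per SD of the score: approximately the same, 0.148.
- Interaction with a binary moderator, proportion p in one subgroup: 0.148 × √(1/p + 1/(1−p)). For p = 0.5 this is 0.148 × 2 = 0.296; for 0.25, 0.148 × 2.309 = 0.342; for 0.20, 0.148 × 2.5 = 0.370.

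**4. Power** (noncentral t, no covariate adjustment).

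| Reading of the interaction | Completers | Power |
|---|---|---|
| Binary, 0.40 between subgroups, 50/50 | 204 | 27% |
| Binary, 0.40, 25/75 | 204 | 21% |
| Binary, 0.40, 20/80 | 204 | 19% |
| Binary, 0.40, 50/50 | 292 (no loss) | 36% |
| Continuous, 0.40 per SD of chronotype | 204 | 77% |
| Continuous, 0.20 per SD | 204 | 27% |

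Hand check of the first row: 0.40/0.296 = 1.35, and Φ(1.35 − 1.96) = 0.27. If covariates correlate 0.5 with the outcome (an assumption), the first row rises to about 34%.

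**5. Interaction detectable with 80% power at 204 completers**, using 1.96 + 0.84 = 2.80.
- Two equal subgroups: 2.80 × 0.296 = about 0.83 SD.
- Continuous score: 2.80 × 0.148 = about 0.41 SD of outcome per SD of chronotype.

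For an even binary split and an interaction of 0.40, the number of completers needed is (7.849/0.16) × (3 + 1.5) × 4 = about 883.

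**6. Allocation ratio.** At fixed N, the variance is proportional to 1/(1/3) + 1/(2/3) = 4.5 under 2:1 and to 2 + 2 = 4 under 1:1. So 2:1 raises it by 4.5/4 − 1 = 12.5% for a moderator measured in both arms.

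**7. Primary comparison.** d = 0.50 with 68.6 + 135.8 completers gives about 92% power under the same simple t-test.

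**The case against.** The best defence is that chronotype is a score and may be analysed as one. For a standardised continuous moderator the interaction has about the same standard error as the arm comparison. If 0.40 means the change in treatment effect per SD of chronotype, the t-test gives roughly the right number: 80% at 224 completers, 77% at 204 and 90% if all 292 are retained. Covariate adjustment could also lift the 204-completer figure above 80%: with r = 0.5, 0.40/(0.148 × 0.866) = 3.12 and Φ(3.12 − 1.96) = 0.88. This stands as a possibility. But the article does not say that 0.40 has that meaning, and it would be a strong moderator: around an average effect of 0.50, the treatment effect would be 0.10 at one SD on one side and 0.90 on the other.

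A reader might therefore infer that true power simply is 20-27%, or that an interaction always has at least four times the variance of a main effect. The documents support neither. Both need a dichotomised chronotype, and the power range also needs 0.40 SD as the gap between subgroup effects, about 204 completers and no covariate gain.

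A reader might also infer that the Randomization statement on increased power should be struck out. That goes too far. The section argues that 2:1 may help recruitment and lets more treatment groups form in limited time, so N is not simply fixed. Treatment group size is also a planned moderator that exists only among treated participants, and there more of them do help.

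Finally, moderation is a secondary aim and two sections already call this work exploratory. That lowers the severity but does not remove the incorrect power statement.

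**Conclusion.** The point holds in this form: 292 is a main-effect sample size labelled as a moderation sample size, and 80% power for moderation by chronotype is not demonstrated. The exact reproduction of 98 + 194 makes this firm.

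The size of the shortfall is conditional. It is large under a dichotomised chronotype with 0.40 SD between subgroups, or a continuous score with 0.20 per SD. It is small or absent under a continuous score with 0.40 per SD. The article does not say which applies. Nothing here weakens the primary comparison, and no change in N is called for. Severity: should-fix.

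**What to change.** - **Sample size:** state that the d = 0.40 t-test powers the comparison of arms, and that 292 does not give a demonstrated 80% power for moderation. Report the detectable interaction on the scale that will be analysed, with its assumptions. At 204 completers without covariate adjustment this is about 0.41 SD of outcome per SD of a continuous score, or about 0.83 SD between two equal subgroups. The two figures must not be interchanged.
- **Aims and Statistical analysis plan:** label moderation as exploratory, in line with the Abstract (Methods) and Background.
- **Abstract (Discussion):** replace the promise to identify who benefits with an intention to explore it.
- **Randomization:** qualify the increased-power statement. It can hold through better recruitment or for moderators that exist only in treated participants; at fixed N, 2:1 costs 12.5% in interaction variance for moderators measured in both arms.

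The cost is wording only. Enrolment, conduct and the primary analysis stay as they are; one stated power claim becomes less favourable.

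### The 292 target, set by the additional chronotype-related calculation, does not allow fully for 30% attrition: it gives about 76% power at d = 0.40, not 80%, while the primary comparison stays above its target

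*Protocol article*

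**What the plan says.** The Sample size section of the protocol article contains two calculations.

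- **Primary comparison.** A two-tailed t-test at 5% with "90% power to detect a medium Cohen’s *d* effect size of 0.50, with an allocation ratio of 2:1". The result is 192 in total, with no attrition allowance mentioned.
- **Additional calculation.** Its stated purpose is "to have sufficient power for moderation analyses of chronotype". The text reads "we carried out a two-tailed t-test with 5% alpha level and 80% power to detect a small to medium Cohen’s *d* effect size of 0.40", again at 2:1, and "accounting for a 30% attrition rate based on dropout rates reported by previous studies". The conclusion is "The final needed sample size was 292 participants (98 in the control group, 194 in intervention group".

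The section prints neither the number of completers needed before attrition nor the inflation formula. The Randomization section confirms the 2:1 ratio. The Methods part of the abstract gives the target as roughly 300.

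**The concern.** If 30% of those randomised are expected to be lost, the number of completers must be divided by 0.7. Multiplying by 1.3 is a common slip, and it leaves too few: 1.3 × 0.7 = 0.91, so only 91% of the required completers remain. The stated total and arm sizes look like the product of that slip.

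The second calculation is the one that raises the target from 192 to 292, so it sets the trial's size. If its inflation is wrong, the sample size and the 80% attached to it do not follow from the section's own inputs. A reader who later relied on that 80%, for example to interpret a null result, would be misled.

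**Working it through.** **Method.** Power of a two-sample t-test from the noncentral t distribution, with n₁ + n₂ − 2 degrees of freedom and noncentrality d × √(n₁n₂/(n₁ + n₂)), two-sided 5%. All inputs come from the Sample size section.

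**1. Reproduce the first calculation.** d = 0.50, 90% power, 2:1. With 64 + 128 = 192 the noncentrality is 0.50 × √(64 × 128/192) = 3.27 and power is 90.1%. This matches the stated 192, so the inputs are being read as the authors read them.

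**2. Completers needed for the second calculation.** d = 0.40, 80% power, 2:1. With 75 + 149 = 224 the noncentrality is 0.40 × √(75 × 149/224) = 2.83 and power is 80.3%. With 74 + 149 power is 79.97%, just short. Exact 2:1 rounding gives 75 + 150 = 225; the normal approximation gives 222.

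**3. Where 292 comes from.**
- Multiplying by 1.3: 75 × 1.3 = 97.5, rounded up to 98; 149 × 1.3 = 193.7, rounded up to 194; total 292. Both arms and the total match the stated figures. Starting from 75 + 150 would give 98 + 195 = 293, one more than stated.
- Dividing by 0.7: 224/0.7 = 320. The range for 222 to 225 completers is 318 to 322.
- Other routes: a one-sided test needs 176 to 177 completers, about 253 after division by 0.7; the 192 of the first calculation divided by 0.7 gives 275. Neither yields 292.

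**4. What 292 delivers at 30% attrition.** 292 × 0.7 = 204.4, that is 98 × 0.7 = 68.6 and 194 × 0.7 = 135.8, or about 68 + 136 = 204.

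| Quantity | Result |
|---|---|
| Power at d = 0.40, 68 + 136 | 76.4% (76.7% with unrounded arms) |
| Smallest d with 80% power, 68 + 136 | 0.418 |
| Attrition at which 224 completers remain | 1 − 224/292 = 23.3% |
| Power at d = 0.40 if 300 are randomised (70 + 140) | 77.6% |
| Power at d = 0.50, 68 + 136 (primary comparison) | 91.8% |

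**5. Shortfall.** 320 − 292 = 28 randomised participants; 224 − 204 = 20 completers; 80 − 76.4 = 3.6 points of power.

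**The case against.** The best defence is that little depends on this, and much of it stands.

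- **The primary outcome.** A reader might infer that the trial's main power claim fails. The document does not support that. The 80% at d = 0.40 belongs to the calculation made for chronotype moderation, which falls under the secondary aims. The primary comparison has its own target of 192, and 204 completers exceed it.
- **Retention and partial data.** The Eligibility and procedure section plans reminders and, as a last step, collection of the ISI alone by phone. The Statistical analysis plan section plans linear mixed models, which can use other visits when the 3-month value is missing. Thirty per cent dropout therefore need not remove all information on 30% of participants. This mitigates the shortfall but does not rebut the error: the calculation is a t-test with an explicit attrition allowance and claims no such recovery.
- **The larger target.** Recruiting 300 narrows the gap: 224 completers remain if attrition is at most 1 − 224/300 = 25.3%. At 30% attrition, power is still 77.6%.
- **The mechanism.** The ×1.3 step is an inference. The agreement of both arms makes it a strong one, and the shortfall does not depend on it: by any route, 292 less 30% is about 204, not 224.

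A further tempting reading is that 76% is the true power of the moderation analysis. It is not, and neither is 80%. A two-group t-test addresses a difference between arm means, not whether that difference varies with chronotype.

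**Conclusion.** The stated sample size does not follow from its own inputs. For 80% power at d = 0.40 with 30% attrition, the section's assumptions require about 320 randomised. The stated 292 gives about 204 completers and about 76% power for a between-arm difference of that size. The gap is beyond rounding, since no variant of the completer count (222 to 225) leads to 292 when divided by 0.7.

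Severity is minor to moderate. The error is confined to the additional calculation and costs under 4 points of power, or a detectable d of 0.42 instead of 0.40. The primary comparison keeps about 92% power at d = 0.50, above its 90% target.

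These power figures assume a completers-only t-test, as in the protocol's own calculation, equal proportional loss in both arms, and independent observations. The last assumption matters because treatment is delivered in groups; no allowance for clustering is included here.

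**What to change.** Keep 292 and replace the statement of the final sample size with wording such as:

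> For the additional calculation made with the chronotype moderation analysis in mind (two-group t-test, d = 0.40), 292 randomised leaves about 204 completers at 30% attrition. This gives about 76% power for a between-arm difference of d = 0.40 (80% for d = 0.42, or 80% for d = 0.40 if attrition is at most about 23%). It is power for a between-arm difference and not for a group-by-chronotype interaction. The primary comparison at d = 0.50 retains about 92% power before any allowance for clustering.

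The cost is a few sentences and a slightly less favourable power statement for a secondary purpose. No extra participants and no change of design are needed. Raising the target to 320 would also restore consistency, at a cost of 28 more participants, but the primary objective does not require it.
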